Family planning is also an important area for health care providers and counselors to discuss with their patients. Approximately half of HIV-positive women sampled in a recent Demographic and Health Survey (DHS) in Kenya and Uganda reported that their last pregnancy was unplanned or unwanted (54% and 49%, respectively; Bunnell, 2007). Further, in Kenya, one factor associated with unplanned pregnancy was unmet need for family planning (Magadi, 2003), and among HIV-positive women who did not want more children the majority (64%) reported that their needs for contraception were not being met (Bunnell, 2007). Given that sexual activity tends to increase as health is restored in HIV-positive persons on antiretroviral therapy (ART; Bunnell et al, 2006a & 2006b), and women report low rates of condom use in relationships (Cleland & Ali, 2006), addressing the family planning needs of HIV-positive persons is essential to reduce the number of unwanted and unplanned pregnancies and ultimately to reduce the number of HIV-positive children. However, a significant proportion of HIV-positive persons choose to have children with their partner (Mpangile et al., 2006; Nakayiwa et al., 2006). For example, in Nigeria among discordant couples, one study found that over half who already had children, as well as all of those who did not, desired and planned to have children in the future (Oladapo et al., 2005). Counseling on safer pregnancies and reducing chances for transmission to children for HIV-positive couples who desire children is also critical for prevention efforts. WHO (2008) strongly encourages counseling and services to prevent unintended pregnancy, foster lower risk pregnancy in those who desire children, and prevent maternal-to-child transmission. While family planning services are available to some HIV-positive women through family planning clinics, providers in family planning clinics may not know the serostatus of their patients or may not have the specialized training and knowledge to meet the particular family planning needs of HIV-positive women and couples. Further, given the added time and transportation burden of another clinic visit, many women do not attend these clinics. To date, family planning services for HIV-positive women have rarely been integrated into HIV care and treatment settings, leaving missed opportunities to offer critical prevention counseling and contraceptives to female patients and couples.

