**Participant exclusion criteria**

Clinic patients

- Younger than 18 years of age
- Not sexually active within the last three months
- Planning to move from the vicinity of the clinic within one year
- Not enrolled in the HIV clinic and/or have not been seen for at least two clinic visits
- Cannot provide informed consent
- Patients who are acutely ill or are determined by clinical staff to be too ill to participate
- Spouses or identified partners of participating patients
- Pregnant women and male partners of pregnant women, as family planning counseling and unintended pregnancy are some of the primary study outcomes
- Not able to complete interview in one of the languages in the inclusion criteria
- Participated in pilot study

Health care providers and lay counselors

- Younger than 18 years of age
- Not fluent/literate in the language selected for the project training
- Planning to leave the clinic within one year
- Not willing to complete project questions
- Do not agree to be observed during patient visits

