**Sampling, including sample size and statistical power**

Participants will be sampled from the database of patients already receiving care at the project clinics. Information about gender, whether on ART, and last clinic visit will be used to create a list of potential participants. From that list, patients will be randomly selected to create a list of patients to approach about participating in the project. When patients arrive at the clinic the list will be checked and if their name is on it they will be asked if they are interested in participating in the project (see enrollment section below for further description). If they are not, their name will be removed from the list. Each clinic will enroll approximately half of each gender and half who are on ART. A tally of persons in each of the gender by ART cells will be kept updated daily. As each of the cells near the enrollment targets the study coordinator will monitor the potential participant list to ensure that appropriate numbers of participants are in each group.

The primary outcome variable for the project will be participant self-report of any unprotected sex in the past 3 months. Prior studies have found rates of condom use to be very low in the areas in which this project will be conducted (Arthur et al., 2007; Feldblum et al., 2000; Kapiga et al., 2006; Mwaluko et al., 2003; Norman, 2003; Stanton et al., 1999; Ross et al., 2007; Watson-Jones et al., 2007). We will assume a rate of at least 50% for any unprotected sex in the past 3 months in the comparison condition for sample size estimation.

Although the proposed project includes measurements at three time points (baseline, 6 months and 12 months), sample size estimates are presented for the simple difference between proportions in the two project conditions at the 12-month follow-up only. This approach is conservative because analytic approaches taking into account the multiple observations on each participant will be more powerful. We use the cross-sectional approach for sample size estimation because no prior data are available on which to base prediction of the pattern of intervention effects over time and the magnitude of the over-time correlation of groups and group members that we can expect in this project. Our sample size estimates do take into account expectations of attrition in the project cohort, which we expect to be moderate (at most 30% at the 12-month follow-up).

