***Health Care Provider-delivered Prevention Messages***

*1) 5 HIV Prevention Steps for PLWHA in HIV Care and Treatment Settings*

and

*HIV Prevention Messages for PLWHA in HIV Care and Treatment Settings*

Background: Delivering prevention messages to HIV-positive individuals in care and treatment settings can significantly impact the HIV transmission risk behavior of infected persons. Two US-based health care provider-delivered interventions involving providers discussing prevention topics (e.g., serostatus disclosure, consistent condom use) were found to be effective at decreasing the rate of unprotected sex in HIV-positive individuals (Fisher et al., 2006; Richardson et al., 2004). In addition, these studies showed that integrating brief prevention discussions into routine clinic visits in busy medical settings was feasible. Training health care providers to routinely deliver prevention messages to HIV-positive patients in care and treatment settings in sub-Saharan African countries may also be an effective prevention strategy to facilitate reduction of sexual risk behaviors. The intervention and materials developed for this project were adapted from Partnership for Health (Richardson et al., 2004). The investigators obtained input from health care providers in Kenya, Uganda, and Botswana for the adaptation of the materials for the African context and field tested the interventions in 3 clinics in Kenya. The original intervention was expanded to include additional prevention messages and services to more comprehensively address prevention for HIV positive persons and to meet the demands of the African setting.

Intervention Components:

HIV health care providers (e.g., doctors, clinical officers, nurses) and professional staff (e.g., social workers, pharmacists) who are involved with the care of HIV infected patients in the HIV clinic will assess prevention issues and deliver specific prevention messages during routine clinic visits. Specifically, providers will do the following:

- Assess whether patient is sexually active
- Assess whether sex partner(s) have been tested for HIV and refer partner(s) for testing
- Assess whether patient has disclosed to sex partner(s) and encourage disclosure
- Encourage adoption of safer sex behaviors (e.g., abstain or be faithful to one partner, reduce number of partners, and use condoms with every sexual encounter)
- Explain the negative consequences of having sex without a condom

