Background: There is a large unmet need for family planning services among HIV-positive women. Most HIV care and treatment clinics do not offer integrated family planning services but refer women to family planning clinics. These clinics are often not equipped to meet the specific needs of HIV-positive women, or may not know the HIV status of the women they are seeing, as many HIV positive women will not disclose their status in another setting. Further, referrals to additional clinics with long queues and waiting times are often deterrents to HIV-positive women who may already be spending a day a month at the HIV clinic for their care and treatment. However, as health is improved due to ARV treatment, many HIV-positive women and their spouses or partners resume sexual activity and have unintended pregnancies, which carry the risk of giving birth to children who are HIV-positive. Alternatively, many couples living with HIV desire children. Counseling on safer pregnancies for women living with HIV and their partners is critical to reduce the chances of transmission to infants. The intervention and materials used in this project were adapted from WHO’s IMAI Reproductive Choices and Family Planning for people living with HIV (WHO, 2006b) in collaboration with WHO. These materials were adapted for the HIV care and treatment setting.

Intervention: HIV providers will ask female patients about their pregnancy status and pregnancy intentions during every routine clinic visit (or the status and intentions of their male patients’ partners). Providers will tailor the counseling and services they offer to the patient’s particular situation. Specifically,

- HIV-positive women who do not desire pregnancy in the near future will be counseled by the provider on dual protection and dual method use and provided with condoms and contraceptive pills or injections, if desired. Providers will refer women who desire longer-acting or more permanent forms of birth control (i.e., IUD, sterilization) to the family planning clinic.
- HIV-positive women who desire pregnancy will be informed by their provider of the risks involved and on safer ways to conceive, with particular emphasis on using condoms except for the most fertile days of the menstrual cycle. In addition, women’s health status and medication regimen will be assessed, and brief guidance on safer pregnancy and delivery to reduce the likelihood of maternal-to-child transmission will be provided.

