**FOR MALES: GO TO QUESTION P1m ON PAGE 38**

**FOR FEMALES ONLY**

P1f. Has anyone in this HIV clinic ever spoken with you about contraceptives or family planning?

_____ 0. No *Skip to P2f*

_____ 1. Yes

*_____-1. Don’t know*

*_____-2. Refused*

P1fa. Which of the following staff at this HIV clinic have ever discussed contraceptives or family planning with you?

_____ 1. Health Care Provider (e.g, Clinical Officer, Doctor)

_____ 2. Nurse

_____ 3. Counselor

_____ 4. Pharmacist

_____ 5. Other (specify) ____________________

*_____-1. Don’t know*

*_____-2. Refused*

P2f. Are you pregnant now?

_____ 0. No

_____ 1. Yes  *Skip to P11f*

*_____-1. Don’t know*

*_____-2. Refused*

P3f. Do you want to get pregnant in the next 6 months?

_____ 0. No

_____ 1. Yes

*_____-1. Don’t know*

*_____-2. Refused*

P4f. Does your spouse or main sex partner want you to get pregnant in the next 6 months?

_____ 0. No

_____ 1. Yes

_____ 2. Don’t have a spouse or main sex partner

*_____-1. Don’t know*

*_____-2. Refused*

P5f. Have you ever used any method to avoid getting pregnant?

_____ 0. No

_____ 1. Yes

*_____-1. Don’t know*

*_____-2. Refused*

P6f. Are you currently using any of these methods to avoid getting pregnant?

|  | **No** | **Yes** | *Don’t know* | *Refused* |
| --- | --- | --- | --- | --- |
| a. Pill | 0 | 1 | -1 | -2 |
| b. IUD (Intra-Uterine Device) | 0 | 1 | -1 | -2 |
| c. Injectable | 0 | 1 | -1 | -2 |
| d. Implants | 0 | 1 | -1 | -2 |
| e. Condom | 0 | 1 | -1 | -2 |
| f. Diaphragm | 0 | 1 | -1 | -2 |
| g. Foam/jelly | 0 | 1 | -1 | -2 |
| h. Lactational amenorrhea | 0 | 1 | -1 | -2 |
| i. Rhythm Method | 0 | 1 | -1 | -2 |
| j. Withdrawl | 0 | 1 | -1 | -2 |
| k. Female Sterilization | 0 | 1 | -1 | -2 |
| l. Male Sterilization | 0 | 1 | -1 | -2 |
| m. Other (Specify) ______________________ | 0 | 1 | -1 | -2 |

 **If NO to ALL of above, then ask P7f. Otherwise Skip** **P8f.**

P7f. I am going to read you some reasons people sometimes give for not using any method to avoid getting pregnant. For each of these, please tell me if this is a reason why you are not using any method.

|  | **No** | **Yes** | *Don’t know* | *Refused* |
| --- | --- | --- | --- | --- |
| a. I want to have children | 0 | 1 | -1 | -2 |
| b. My partner or I cannot get pregnant | 0 | 1 | -1 | -2 |
| c. I do not like the side effects of contraceptives | 0 | 1 | -1 | -2 |
| d. Contraceptives are inconvenient | 0 | 1 | -1 | -2 |

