**FOR MALES ONLY**

| ***Interviewer reads:***“Now I am going to ask you questions about pregnancy, family planning, and your desire for children with your main partner.” |
| --- |

P1m. Has anyone in this HIV clinic ever spoken with you about contraceptives or family planning?

_____ 0. No *Skip to P2m*

_____ 1. Yes

*_____-1. Don’t know*

*_____-2. Refused*

P1ma. Which of the following staff at this HIV clinic have ever discussed contraceptives or family planning with you?

_____ 1. Health Care Provider (e.g, Clinical Officer, Doctor)

_____ 2. Nurse

_____ 3. Counselor

_____ 4. Pharmacist

_____ 5. Other (specify) ____________________

*_____-1. Don’t know*

*_____-2. Refused*

P2m. Is the person you consider to be your spouse or main partner currently pregnant?

_____ 0. No

_____ 1. Yes  *Skip to P8m*

_____ 2. No main partner  *Skip to Q1 in next section*

*_____-1. Don’t know*

*_____-2. Refused*

P3m. Do you want her to get pregnant in the next 6 months?

_____ 0. No

_____ 1. Yes

*_____-1. Don’t know*

*_____-2. Refused*

P4m. Does your spouse or main partner want to get pregnant in the next 6 months?

_____ 0. No

_____ 1. Yes

*_____-1. Don’t know*

*_____-2. Refused*

P5m. Have you ever used any method to avoid getting your spouse or partner(s) pregnant?

_____ 0. No  *Skip to P7m*

_____ 1. Yes

*_____-1. Don’t know*

*_____-2. Refused*

P6m. Are you, your spouse, or your main sex partner currently using any of these methods to avoid getting pregnant?

|  | **No** | **Yes** | *Don’t know* | *Refused* |
| --- | --- | --- | --- | --- |
| a. Pill | 0 | 1 | *-1* | *-2* |
| b. IUD (Intra-Uterine Device) | 0 | 1 | *-1* | *-2* |
| c. Injectable | 0 | 1 | *-1* | *-2* |
| d. Implants | 0 | 1 | *-1* | *-2* |
| e. Condom | 0 | 1 | *-1* | *-2* |
| f. Diaphragm | 0 | 1 | *-1* | *-2* |
| g. Foam/jelly | 0 | 1 | *-1* | *-2* |
| h. Lactational amenorrhea | 0 | 1 | *-1* | *-2* |
| i. Rhythm Method | 0 | 1 | *-1* | *-2* |
| j. Withdrawl | 0 | 1 | *-1* | *-2* |
| k. Female Sterilization | 0 | 1 | *-1* | *-2* |
| l. Male Sterilization | 0 | 1 | *-1* | *-2* |
| m. Other (Specify) ______________________ | 0 | 1 | *-1* | *-2* |

 **If NO to ALL of above, then ask P7m. Otherwise Skip** **P10m.**

P7m. I am going to read you some reasons people sometimes give for not using any method to avoid getting pregnant. For each of these, please tell me if this is a reason why you and your partner are not using any method.

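### The any/none primary outcome cannot show partial risk reduction in participants who follow the package's safer-conception advice, so the overall contrast may be diluted towards no effect

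*Protocol*

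**What the plan says.** **Outcome.** Protocol, Sampling, including sample size and statistical power: "The primary outcome variable for the project will be participant self-report of any unprotected sex in the past 3 months". The power summary and the shells of Tables 3 and 4 use the same variable. No exception is made for attempts to conceive.

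**Counselling.** The general provider messages include "use condoms with every sexual encounter". The family planning component tailors advice to pregnancy intention. Women who desire pregnancy are told of the risks and counselled on "safer ways to conceive, with particular emphasis on using condoms except for the most fertile days of the menstrual cycle". Male patients are counselled or referred according to the couple's intentions.

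**Who is enrolled.** The exclusion criterion is current pregnancy: "Pregnant women and male partners of pregnant women, as family planning counseling and unintended pregnancy are some of the primary study outcomes". Desire for pregnancy does not exclude anyone. The literature review says that "a significant proportion of HIV-positive persons choose to have children with their partner", but gives no figure for this cohort.

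**What is collected and used.** Appendix H asks women "P3f. Do you want to get pregnant in the next 6 months" and men with a main partner "P3m. Do you want her to get pregnant in the next 6 months". It also counts acts and condom-protected acts per partner over 90 days (items J24-J25 and J29-J30). The initial primary model in the Data analysis plan contains the baseline outcome, country, condition, time and their interactions. Pregnancy intention is not in it.

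**The concern.** One arm receives advice that, when followed, produces a positive score on the primary outcome.

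- A woman who moves from no condom use to condoms on all but the fertile days scores 1 before and 1 after. Her reduction in exposure is not seen.
- A patient who always used condoms and then follows the conception advice moves from 0 to 1 and is recorded as worse.

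Both pull the comparison between arms towards no effect. This happens even if the arms are perfectly balanced on pregnancy intention, so the planned adjustment for baseline differences does not address it. At stake is the reading of a weak or null primary result, which the protocol intends to use in scale-up decisions.

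**Working it through.** **Inputs from the protocol.** Comparison rate .50; intervention rate .375 (25% relative, 12.5 points); ICC .01 and .02; g = 9 clinics per condition; m = 140 retained per clinic (200 enrolled, 30% loss); two-sided α = .05. The power formula is rebuilt from the terms the protocol defines:

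variance of the difference = [p1(1−p1) + p2(1−p2)] × [1 + (m−1) × ICC] / (m × g), tested on t with 2(g−1) = 16 df (critical value 2.120); power from the noncentral t.

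**Step 1. The plan's own figure.** At ICC .02 the design effect is 1 + 139 × .02 = 3.78. The variance is (.25 + .2344) × 3.78 / 1260 = .001453, so SE = .0381 and .125 / .0381 = 3.28. Power is 86.8%. At ICC .01 (design effect 2.39) it is 97%. The claim of at least 80% holds.

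**Step 2. Dilution.** Assume a share f desires pregnancy, has rate r of any unprotected sex in both arms, and shows no arm difference. Everyone else improves by the full 25%. The overall comparison rate stays at .50. Then

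p2 = .50 − .25 × (.50 − f × r).

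Example, f = .20 and r = .50: p2 = .50 − .25 × .40 = .40. At ICC .02 the variance is (.25 + .24) × 3.78 / 1260 = .00147, SE = .0383, ratio 2.61, power 69%.

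| Share f | Rate r | p2 | Relative reduction | Power, ICC .02 | Power, ICC .01 |
| --- | --- | --- | --- | --- | --- |
| 5% | .50 | .381 | 23.8% | 83% | 96% |
| 10% | .50 | .3875 | 22.5% | 79% | 93% |
| 20% | .50 | .400 | 20.0% | 69% | 87% |
| 30% | .50 | .4125 | 17.5% | 57% | 77% |
| 10% | .70 | .3925 | 21.5% | 75% | 91% |
| 20% | .70 | .410 | 18.0% | 60% | 79% |
| 30% | .70 | .4275 | 14.5% | 42% | 60% |

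With r = .50, power drops below 80% once f exceeds about 8% at ICC .02, or about 27% at ICC .01. If the advice also moved consistent condom users from 0 to 1, the contrast would shrink further. The protocol gives no basis for putting a figure on that.

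The share f, the rate r and the absence of any response in this group are assumptions. None is in the protocol.

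**Step 3. Can the collected item identify the affected group?** By the Study timeline, baseline is January-February 2009, so the 6-month horizon of P3f and P3m ends about July-August 2009. The 12-month interviews are in April-May 2010, and their 3-month recall starts about January 2010. The two periods do not overlap. The recall of the 6-month interviews (September-October 2009) overlaps the horizon only in part. Follow-up answers are incomplete because women who are then pregnant skip P3f, and men with a pregnant partner or no main partner skip P3m. Baseline intention is therefore the cleaner variable, but only a partial marker.

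**The case against.** **The outcome is not mis-scored.** It asks whether unprotected sex occurred, and in both examples it did. The protocol aims at transmission risk behaviours, so counting that exposure under intention to treat is legitimate. This stands. The limitation is that any/none cannot show a reduction short of zero.

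**The power claim does not assume that everyone responds.** A reader might infer from Step 2 that the stated power is wrong or lost. The protocol powers a marginal difference of .50 against .375, and .375 can already average responders and non-responders. At that difference power is 86.8%. This stands. Step 2 shows only what follows if the 25% is achieved solely outside this group.

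**The size is assumed.** A small share, or ICC .01, leaves power at or near 80% or above. The protocol also calls its cross-sectional calculation conservative because repeated measures should add power. That stands, though extra precision does not restore a diluted effect estimate. It is also too strong to say that this group cannot respond: plans can change, or conception can occur, before the 12-month window.

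**Partial credit already exists.** The Variables section lists the proportion of acts unprotected with HIV-negative or unknown-status partners among the outcomes. This answers part of the point. That measure is not the powered variable, is not linked to pregnancy intention, and leaves out partners known to be HIV-positive.

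**These are analysis-plan details.** Covariates and supporting analyses may properly sit in a statistical analysis plan, which was not available here. The tension itself, between outcome and advice, is in the protocol.

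**Conclusion.** The point holds as a limit on interpretation. The primary outcome and the safer-conception advice pull in opposite directions for participants who desire pregnancy. These participants can be enrolled, and the stated primary model does not use the intention data collected. The direction of the effect is towards no benefit. Its size is unknown: under the assumptions of Step 2 with a 50% rate in this group, power runs from 83% down to 57% at ICC .02 and from 96% down to 77% at ICC .01, for shares of 5% to 30%. It is lower if that group's rate is higher.

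The documents do not support three stronger readings: that the sample size is wrong, that the outcome misclassifies participants, or that the stated power is lost. No view is taken on the counselling itself.

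**What to change.** Keep the outcome and the counselling unchanged. Before follow-up data are analysed for intervention effects, add to the analysis plan:

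1. Baseline pregnancy intention (P3f/P3m, with no main partner as its own category) as a covariate in the primary model. This is for precision. A main-effect covariate does not cure dilution.
2. The same model among participants not wanting pregnancy at baseline, reported beside the overall result. State that the item covers only the next 6 months and so identifies conception attempts in the 12-month window imperfectly.
3. The proportion of unprotected acts (J24-J25 and J29-J30), by baseline intention, as a supporting analysis alongside the proportion measure already listed under Variables.

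**Cost.** Wording only, with no new data. The protocol says the 6- and 12-month data will not be examined for intervention effects during the project, so there is time to prespecify. The restricted analysis has fewer participants and only partly separates the affected group. With a 20% share and a 70% rate in that group, the others' rates are (.50 − .20 × .70) / .80 = .45 against .3375, with m = 112. Power at ICC .02 is then about 78%, against 60% for the diluted overall contrast. That figure assumes the baseline item identifies the group perfectly, which Step 3 shows it does not.

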In the following sample size table, we present calculations for the number of clinics needed for at least 80% power to detect differences of varying size between the intervention and comparison conditions with a two-sided test and α=0.05. Sample size estimates are based on a formula in Murray (1998) for group-randomized trials:

Where g is the number of groups per condition, and are the event rates in the two project conditions, *m* is the number of members per group (clinic), is the intraclass correlation coefficient measuring the correlation of members nested within groups, nested within project conditions, and and are critical values from the t-distribution.

Table 1 presents the sample sizes necessary for at least 80% power to detect a 20-30% reduction in the rate of unprotected sex in the past 3 months in the treatment condition compared to the comparison condition at the 12-month follow-up. We use 50% as the rate of unprotected sex in the comparison condition for sample size estimation; if the actual rate is higher or lower with the same reduction in the treatment condition, power will be greater, as variance in the binomial distribution is largest at 50% and decreases as the event rate moves away from 50% in either direction. Power calculations for group-randomized trials also need to take the expected intraclass correlation coefficient (ICC) into account to have adequate power. However, there are no prior published reports of ICCs for sexual risk behaviors among clinic attendees in sub-Saharan Africa on which to base our power calculations. A prior study did report an ICC of .0011 for STI prevalence at the community level in Kenya (Feldblum et al., 2000), and another study presented an ICC of about .01 for any unprotected sex in the past 90 days in a neighborhood-randomized trial in the U.S. (Pals et al., 2008). ICCs are generally larger for behavioral variables than for biologic variables and also generally increase as the group size decreases (e.g. larger for clinics than for communities). Murray and Blitstein (2003) showed that including multiple timepoints in analytic models can substantially reduce the ICC. Based on these prior results, we use ICCs of .01 and .02 for sample size estimation.

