**Table 1. Number of groups and members per condition needed for at least 80% power to detect a 20-30% difference between intervention and comparison conditions in report of any unprotected sex in the past 3 months (assuming intraclass correlations of 0.01 or 0.02).**

| **P1** | **P2** | | **ICC** | **Absolute Difference** | **% Difference** | **Members per group enrolled** | **Members per group retained** | **Number of groups needed per condition** |
| --- | --- | --- | --- | --- | --- | --- | --- | --- |
| .50 | .3875 | | .01 | .1125 | 22.5 | 200 | 140 | 7 |
| .50 | .3750 | | .01 | .1250 | 25 | 200 | 140 | 6 |
| .50 | .3625 | | .01 | .1375 | 27.5 | 200 | 140 | 5 |
| .50 | .3500 | | .01 | .1500 | 30 | 200 | 140 | 4 |
| .50 | | .3750 | .02 | .1250 | 25 | 200 | 140 | 9 |
| .50 | | .3625 | .02 | .1375 | 27.5 | 200 | 140 | 7 |
| .50 | | .3500 | .02 | .1500 | 30 | 200 | 140 | 6 |

P1=proportion reporting any unprotected sex in the comparison group; P2=proportion reporting any unprotected sex in the intervention group

Table 1 shows that with 9 clinics per condition, each with 200 patients enrolled, the project would have at least 80% power to detect a 25% difference between intervention and comparison (absolute difference of 12.5%) with an ICC of 0.02. If the ICC is smaller or the intervention effect larger, power will be greater then 80%.

Summary

We anticipate enrolling 200 patients per clinic with 9 clinics per condition (3 per condition per country), for a total of 18 clinics and approximately 3600 patients (at least 2520 retained at 12 months). Power calculations demonstrate that this number of participants will allow us at least 80% power to detect a 25% relative difference between conditions for the primary outcome variable of any unprotected sex during the past 3 months, allowing for up to 30% loss to follow-up.

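### For the protocol's own target, a 25% relative reduction, power falls rather than rises when the comparison rate is below 50%; at ICC .02 it drops under 80% at a rate of about 45%

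*Protocol*

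**What the plan says.** All of this is in the Protocol, under Sampling, including sample size and statistical power, unless noted.

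- **Planning rate.** The text first says "We will assume a rate of at least 50% for any unprotected sex in the past 3 months in the comparison condition", and then "We use 50% as the rate of unprotected sex in the comparison condition for sample size estimation".
- **Scale of the effect.** Table 1 is introduced as covering reductions of 20 to 30% in the rate, which is a relative scale. The table has both an absolute and a percentage difference column.
- **The sentence at issue.** Directly after that introduction: "if the actual rate is higher or lower with the same reduction in the treatment condition, power will be greater". The reason given is that binomial variance is largest at 50%.
- **The claim that rests on it.** The Summary says that the planned numbers will "allow us at least 80% power to detect a 25% relative difference between conditions for the primary outcome variable". The same statement stands under Outcomes and minimum meaningful differences. Neither place names the comparison rate or the ICC. The text directly under Table 1 does give the 12.5-point difference and ICC 0.02.

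**The concern.** The variance argument considers only half of the calculation. Power depends on the difference divided by its standard error. If the relative reduction is held at 25%, the difference is 0.25 × P1, so it falls in direct proportion to the comparison rate P1. The variance changes little near 50%, and the standard error moves only with its square root. Power must therefore fall as P1 falls, which is the opposite of the assurance.

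At stake is how the power claim is read. The sentence presents 50% as a worst case. In the downward direction it is the assumption on which the 80% depends. If the 12-month comparison rate came in well below 50% and the result were null, someone relying on the protocol could take the trial to have been adequately powered for its stated target when it was not.

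**Working it through.** **Inputs (Protocol, sampling section and Table 1).** Test: "with a two-sided test and α=0.05". Goal: "calculations for the number of clinics needed for at least 80% power to detect differences of varying size". P1 = .50, P2 = .375, g = 9 clinics per condition, m = 140 retained (200 less 30%), ICC .02 for the design row, t critical values.

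**Formula.** The displayed formula is not legible in the text at hand. The listed symbols point to the usual group-randomized form, which I assume:

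g = [P1(1−P1) + P2(1−P2)] × [1 + (m−1)ICC] × (t_α/2 + t_β)² / [m (P1−P2)²]

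**Step 1: reproduce the plan.** At P1 = .50 and P2 = .375 the variance sum is .2500 + .2344 = .4844. The design effect is 1 + 139 × .02 = 3.78. With 10 df, t_α/2 + t_β = 2.228 + 0.879 = 3.107, so

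g = .4844 × 3.78 × 3.107² / (140 × .125²) = 8.08, rounded up to 9.

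A fixed 9 or 10 df reproduces all seven rows of Table 1 (7, 6, 5, 4, 9, 7, 6). The planned number of clinics therefore stands at its stated inputs.

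**Step 2: power at g = 9.**

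SE = √{.4844 × 3.78 / (140 × 9)} = .0381; noncentrality = .125 / .0381 = 3.28.

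With 2(9−1) = 16 df and the noncentral t, power is 86.8%. With 9 or 10 df it is 83 to 84%. The claim of at least 80% holds at P1 = .50 either way.

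**Step 3: vary P1 with P2 = 0.75 × P1 (ICC .02, 16 df).**

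| P1 | Difference | Variance sum | SE | Noncentrality | Power |
|---|---|---|---|---|---|
| .60 | .1500 | .4875 | .0382 | 3.92 | 95.7% |
| .55 | .1375 | .4898 | .0383 | 3.59 | 92.0% |
| .50 | .1250 | .4844 | .0381 | 3.28 | 86.8% |
| .45 | .1125 | .4711 | .0376 | 2.99 | 80.2% |
| .40 | .1000 | .4500 | .0367 | 2.72 | 72.4% |
| .35 | .0875 | .4211 | .0355 | 2.46 | 63.8% |
| .30 | .0750 | .3844 | .0340 | 2.21 | 54.6% |

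From P1 = .50 to .40 the difference falls by 20%, while the SE falls from .0381 to .0367, about 4%. That is the whole mechanism.

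**Step 4: where power crosses 80%.**

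| ICC | 16 df | 9 to 10 df (reproduces Table 1) |
|---|---|---|
| .02 | P1 ≈ .449 | P1 ≈ .47 to .48 |
| .01 | P1 ≈ .333 | P1 ≈ .35 to .36 |

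At ICC .01 and 16 df, power is 94% at P1 = .45, 89% at .40 and 83% at .35.

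**Step 5: the other reading, a fixed 12.5-point difference (ICC .02, 16 df).** Power is 94.9% at P1 = .30, 89.8% at .40 and 86.8% at .50. The variance sum peaks where the arms straddle 50% (.5625 against .4375), and there power is 86.3%. The dip is half a point and nowhere near 80%.

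**The case against.** The best defence is that the sentence meant a fixed absolute difference. Its reasoning is about variance alone, Table 1 has an absolute difference column, and on that scale the sentence is right at every lower rate. This stands as arithmetic. A reader might go further and say that the sentence fails on the absolute scale too, because of the dip just above 50%. At half a point that is negligible and should not be argued. What the defence cannot remove is that the sentence directly before speaks of a percentage reduction in the rate, and that the stated target is a relative difference.

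The second defence is that the rate is unlikely to be low. The protocol assumes at least 50%, the background section cites condom use of 4 to 28% at the most recent sex act, and entry requires sexual activity in the past three months. Above 50%, with a relative effect, the sentence is correct. This also stands: no figure in the protocol puts the rate below 45%. But the cited condom figures are not specific to patients in HIV care. Participants reporting no sex at follow-up skip the condom items and would presumably count as having no unprotected sex. A lower rate is possible, and it is exactly the case for which the sentence offers reassurance.

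Two stronger inferences are tempting and not supported.

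- **That the trial is too small.** The design row reproduces at its stated inputs.
- **That repeated measures are credited twice.** The 12-month-only calculation is defended with "This approach is conservative because analytic approaches taking into account the multiple observations on each participant will be more powerful", and the ICC choice with "including multiple timepoints in analytic models can substantially reduce the ICC. Based on these prior results, we use ICCs of .01 and .02". The chosen .01 and .02 lie at or above both cited values (.0011 and about .01), so no numerical discount for repeated measures is visible. The conservative wording can stay.

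The mismatch between the announced 20 to 30% range and a lowest table row of 22.5% is a label slip with no bearing on this point.

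**Conclusion.** The assurance about lower comparison rates is wrong on the scale of the protocol's own target. At ICC .02, the value on which the 80% statement rests, power for a 25% relative reduction falls from about 87% at a 50% rate to 72% at 40% and 55% at 30%. It drops below 80% under a rate of about 45%, or 47 to 48% with the degrees of freedom that match Table 1. At ICC .01 the crossing is about 33%, so the 45% figure must always be quoted with its ICC.

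These results assume 9 clinics per arm, 140 retained in each, unpooled binomial variance and the formula inferred above. They do not show that the rate will be low, nor that the number of clinics is wrong. The error is in a statement about robustness and in two summaries that omit their conditions. Severity is moderate: it affects how the power claim is read, not the design, endpoint or analysis.

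**What to change.** 1. Replace the sentence. Say that for a fixed relative reduction power falls as the comparison rate falls below 50% and rises above it. If the variance argument is kept, limit it to a fixed absolute difference.
2. In the Summary of the sampling section and under Outcomes and minimum meaningful differences, add the conditions: comparison rate 50% (12.5-point difference) and ICC .02. If a lower bound for the rate is given instead, about 45% applies with 16 df and 47 to 48% with the df behind Table 1, so state the df as well.
3. Add rows to Table 1, or one line of power figures, for comparison rates of .35 to .45 at ICC .01 and .02.

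The sample size, the number of clinics and the conservative wording need no change. The cost is a few lines of protocol text and a stated power that looks less favourable at lower rates.
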